**Figure 2 F2:**
[figure not shown]
Outline of study protocol. At the end of study follow-up, participants will also complete a survey assessing satisfaction with the discontinuation strategy. 6MWD, 6-min walking distance; CPET, cardiopulmonary exercise testing; FC, functional class; QoL, quality of life; RHC, right heart catheterisation; TTE, transthoracic echocardiogram.

A predefined safety evaluation is performed at week 8 (±3 weeks). Clinical worsening is defined as the simultaneous occurrence of all three of the following criteria: (1) >15% decrease in 6MWD, (2) progression to WHO functional class III/IV, and (3) increase in NT-proBNP of ≥30% to a level of ≥300 pg/mL. This definition is adapted from prior pulmonary arterial hypertension (PAH) and CTEPH trials and aligns with criteria used in the STELLAR trial.^3
15–18^ If clinical worsening is confirmed, TTE is performed and riociguat is reinitiated in the discontinuation group. Unscheduled evaluations may be performed at the investigator’s discretion in case of suspected clinical deterioration.

At study completion, participants complete a survey assessing satisfaction with the discontinuation strategy. Riociguat may be reintroduced after the end-of-study RHC at the discretion of the treating physician and patient.

### Objectives and endpoints

The primary endpoint is the between-group difference in mPAP at rest, measured by RHC at 16 weeks. Secondary endpoints for the primary study objective are outlined in table 1.

**Table 1 T1:** Secondary outcomes for the primary study objective

Objectives	Secondary endpoints
To investigate if discontinuation of riociguat is non-inferior to its continuation in CTEPH patients with mPAP <30 mmHg post-BPA	Efficacy endpoints: Between-group differences at 16 weeks for the following parameters in hierarchical order: NT-proBNP (assessed for non-inferiority) 6MWD (assessed for non-inferiority) PVR Cardiac index Between-group differences at 16 weeks in exercise capacity in post hoc analysis: CPET variables: oxygen uptake, workload, heart rate, respiratory exchange ratio, ventilation, oxygen saturation, oxygen pulse, equivalent carbon dioxide Change in modified Borg dyspnoea scale Safety endpoints: Between-group differences at 16 weeks in the following parameters: Number of adverse events and severe adverse events Proportion of participants with mPAP ≥38 mmHg at RHC Proportion of participants meeting the clinical worsening criteria at week 8 Feasibility of the strategy: Is TTE sufficient to replace RHC at the end of study follow-up? The correlation between TTE and RHC parameters Right ventricular systolic pressure Tricuspid annular plane systolic excursion Proportion of participants missed by TTE with mPAP ≥38 mmHg at 16 weeks RHC Is the discontinuation strategy feasible for implementation in clinical practice? Proportion of participants missed by the clinical worsening criteria with mPAP ≥38 mmHg at 16 weeks Participants' satisfaction with the protocol

BPA, balloon angioplasty; CPET, cardiopulmonary exercise testing; CTEPH, chronic thrombo-embolic pulmonary hypertension; mPAP, mean pulmonary artery pressure; 6MWD, 6-min walking distance; NT-proBNP, N-terminal pro-B-type natriuretic peptide; PVR, pulmonary vascular resistance; RHC, right heart catheterisation; TTE, transthoracic echocardiography; WHO, world health organisation.

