### Interventions

Participants allocated to the control group continue riociguat at the pre-inclusion dose, administered three times a day in accordance with current clinical guidelines.^5
6^ Dose adjustments for hypotension or adverse effects are permitted at the discretion of the treating physician. Participants allocated to the intervention group discontinue riociguat following a structured tapering schedule over 6 days. Treatment is reduced from 2.5 mg three times a day to 2.0 mg three times a day for 2 days, followed by 1.0 mg three times a day for 2 days, after which the medication is discontinued. Participants receiving a lower dose at baseline will enter the tapering schedule at the corresponding step and may skip preceding dose-reduction steps. In case of clinical worsening during follow-up, riociguat is re-initiated at 1.0 mg three times a day for 2 weeks, followed by up-titration to the pre-inclusion dose as tolerated, in accordance with clinical guidelines.^5
6^

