### Follow-up and safety monitoring

The study protocol is outlined in figure 2. Baseline assessments include RHC, cardiopulmonary exercise testing, 6MWD with Borg dyspnoea score, TTE, laboratory testing (including N-terminal pro-BNP (NT-proBNP)), and quality of life questionnaires. These assessments will be repeated at 16 weeks (end of study). Monthly follow-up is performed by outpatient visits or telephone contact to assess symptoms, medication adherence and adverse events (AEs). AEs are collected using open-ended and structured queries, including predefined symptoms such as dizziness and diarrhoea. Blood pressure is measured at each contact; hypotension (≤90/60 mmHg) is graded (grade 1–5) according to Common Terminology Criteria for Adverse Events (CTCAE) v5.0.^14^ Participants have 24/7 access to their PH care team.

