### Analysis set

The primary analysis will be conducted in the per-protocol population, as an intention-to-treat (ITT) analysis can be considered anticonservative in a NI study testing discontinuation. Participants who restart riociguat due to clinical worsening will be analysed in the continuation group. As a secondary analysis, we will perform an ITT analysis according to randomised allocation, reflecting the clinical discontinuation strategy including re-initiation and testing the safety of the stopping strategy. In addition, two exploratory analyses will be performed: a modified ITT analysis excluding participants who restarted riociguat from the discontinuation group to explore outcomes among patients who tolerate treatment withdrawal without re-initiation, and a subgroup analysis comparing participants who restarted riociguat with the continuation group to assess haemodynamic response following re-initiation. Non-compliant patients who meet protocol violations will be excluded as part of the modified per-protocol (PP) analysis. Missing data will not be imputed. However, participants who withdraw before the week 8 clinical worsening assessment because of clinical deterioration, or for whom the reason for withdrawal is unknown, will be conservatively classified as having experienced clinical worsening.

To account for potential loss of participants from the primary per-protocol analysis due to clinical worsening, predefined scenarios were incorporated into the statistical analysis planning. Based on power simulations, the study is expected to retain approximately 80% power if up to 35% of participants are lost from the intervention group. To mitigate the risk of insufficient power, the randomisation ratio will be reassessed after inclusion of 50% of the planned sample size. If ≥30% or ≥40% of participants in the discontinuation group have restarted riociguat at that point, the randomisation ratio will be adaptively adjusted from 1:1 to 2:1 or 3:1, respectively, in favour of the discontinuation group. If ≥50% of participants in the discontinuation group experience clinical worsening, the study will be terminated for safety reasons, as such a rate is considered clinically unacceptable.

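### The clinical-worsening safety endpoint and its withdrawal rule stop at the week-8 visit of a 16-week trial, so later events are left out of this endpoint

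*Protocol article*

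**What the plan says.** Table 1 of the protocol article opens its safety block with "Safety endpoints: Between-group differences at 16 weeks in the following parameters". The third item in that block is the "Proportion of participants meeting the clinical worsening criteria at week 8". Heading and item therefore give different time points.

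The Follow-up and safety monitoring section places the safety evaluation at week 8 with a window of three weeks either side. It sets a strict definition: "Clinical worsening is defined as the simultaneous occurrence of all three of the following criteria". The three are a fall in 6MWD, progression in WHO functional class and a rise in NT-proBNP. The same section allows unscheduled evaluations when deterioration is suspected.

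The Interventions section does not tie worsening to week 8: "In case of clinical worsening during follow-up, riociguat is re-initiated".

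The Analysis set section says that missing data are not imputed, with one conservative exception: "participants who withdraw before the week 8 clinical worsening assessment because of clinical deterioration, or for whom the reason for withdrawal is unknown" are classed as having worsened. No matching rule covers withdrawal between the week-8 visit and week 16.

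**The concern.** Worsening is treated as something that can happen throughout follow-up when it triggers a restart, but as something seen only at one mid-trial visit when it is counted as an endpoint. A participant in the discontinuation arm who meets the criteria at week 12 and restarts does not enter the worsening proportion. A participant who withdraws at week 12 because of deterioration does not enter it either.

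The trial asks whether stopping is safe. This proportion is the only between-group comparison of the three-part worsening definition. If it stops at about half of follow-up, a reader of the results could take a low week-8 figure as the worsening rate of the strategy over 16 weeks.

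**Working it through.** The plan states no expected worsening rate and no power for this endpoint, so there is no figure of its own to reproduce. The check sets the provisions side by side and adds the arithmetic that the stated visit window allows.

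**1. Are the components available after week 8?**
- 6MWD and NT-proBNP: baseline assessments, repeated at week 16 (Follow-up and safety monitoring).
- WHO functional class: compared between groups at week 16 (Table 2).

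All three exist at week 16, so the criteria could be applied there without a new visit or test.

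**2. What happens to a late event under the plan as written?**

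| Participant in the discontinuation arm | Worsening proportion | Primary per-protocol analysis | Other analyses |
|---|---|---|---|
| Meets criteria at week 12 and restarts | Not counted | Analysed in the continuation group | Kept as randomised in ITT; excluded from modified ITT; in the restarter subgroup |
| Withdraws at week 12 for deterioration, no week-16 assessment | Not counted, and not reclassified | No week-16 mPAP, not imputed | No week-16 6MWD or NT-proBNP; adverse events up to withdrawal remain |
| Meets criteria first at week 16 | Not counted | Included with week-16 mPAP | Included in the separate week-16 comparisons |

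**3. How much calendar time is outside the count?** The visit falls between weeks 8 − 3 = 5 and 8 + 3 = 11.
- Visit at week 5: 16 − 5 = 11 weeks uncounted, 11/16 = 69%.
- Visit at week 8: 16 − 8 = 8 weeks, 8/16 = 50%.
- Visit at week 11: 16 − 11 = 5 weeks, 5/16 = 31%.

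**4. Illustration of events, on an assumption.** Assume a constant hazard and a cumulative 16-week risk p of 10% to 35% in an arm of 74/2 = 37. The share of events after week w is 1 − [1 − (1 − p)^(w/16)]/p.

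| Visit week | Share missed, p = 10% | Share missed, p = 35% | Participants missed of 37 |
|---|---|---|---|
| 5 | 68% | 64% | 2.5 to 8.3 |
| 8 | 49% | 45% | 1.8 to 5.8 |
| 11 | 30% | 27% | 1.1 to 3.5 |

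For example, with p = 10% and w = 8: 1 − 0.90^0.5 = 0.051, and 1 − 0.051/0.10 = 0.49. Neither the hazard shape nor p comes from the document.

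**5. Withdrawals, on an assumption.** The Sample size calculation section allows 10% dropout: 0.10 × 74 = 7.4 participants. Spread evenly over 16 weeks, 7.4 × 8/16 = 3.7 fall after week 8 (5.1 after week 5, 2.3 after week 11). This is dropout for all reasons in both arms. Those leaving for deterioration or an unknown reason can only be fewer or equal.

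**The case against.** The strongest defence is that the week-8 endpoint has a purpose of its own. It describes how the scheduled mid-trial safety check performs, with the same timing in both arms. At week 16, catheterisation measures the haemodynamic result directly, and the withdrawal rule is consistent with the endpoint it feeds. That stands as a reason to keep the week-8 proportion. It does not explain why no endpoint counts worsening over the rest of follow-up, or why the item sits under a 16-week heading.

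Several stronger readings are tempting, and the document does not support them.
- A reader might infer that late deterioration goes unrecorded. It does not: adverse events are collected monthly, and mPAP ≥38 mmHg, 6MWD, NT-proBNP and functional class are compared at week 16. Restarts are handled in several analyses without a time limit. Only the composite and the withdrawal classification stop early.
- A reader might take this as the trial's main clinical safety endpoint. It is the third of three listed safety items, unpowered and outside the hierarchy.
- A reader might conclude that the feasibility item on participants with mPAP ≥38 mmHg missed by the criteria is distorted. That item gives no time point for the criteria. Read as week 8, a case detected at week 14 would be labelled missed; read as any time in follow-up, it would not. The item is ambiguous, no more.
- A reader might say that half the events are lost, mostly in the discontinuation arm. The first needs even accrual. The taper takes 6 days, so participants who stop are off the drug early, and nothing in the document supports a constant hazard over 16 weeks. Re-initiation after stopping is by its nature confined to the discontinuation arm, but no figure shows how late withdrawals will divide.

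The article is also a condensed account, and a fuller document may deal with later withdrawals. That could close the withdrawal gap, but it does not alter the explicit week-8 wording of the endpoint.

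**Conclusion.** The point holds for two provisions: the composite worsening endpoint and the rule that classes withdrawals as worsening. Both stop at a visit that may fall anywhere from week 5 to week 11, although worsening can be declared throughout follow-up and its components are measured again at week 16. The effect is that this endpoint can understate harm from stopping. The gap matters most for a late withdrawer, who may have no week-16 data and is not imputed, and for a late restarter, who is moved to the continuation group in the primary analysis.

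The calendar time outside the count, 5 to 11 of 16 weeks, follows from the document. The number of events missed does not, and the figures under a constant hazard are an illustration only. An effect in favour of non-inferiority through late withdrawals would require them to fall mainly in the discontinuation arm, which is plausible but not shown. The primary test, its margin and the sample size are not in question here.

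**What to change.** Make three changes of wording.

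1. Define the safety endpoint as the proportion of participants meeting the existing three-part criteria by week 16, applied in both arms at the week-8 evaluation, at any unscheduled evaluation and at week 16. Keep the week-8 proportion as a supporting figure. Because unscheduled evaluations are discretionary and the trial is open-label, report how many events came from each type of evaluation.
2. Extend the existing withdrawal classification to withdrawals before the week-16 assessment, still limited to deterioration or unknown reason. Extending it to every withdrawal would go beyond the present rule and would count people who left for a known, unrelated reason.
3. State that the feasibility item on cases missed by the criteria uses the criteria at any time up to week 16.

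The re-initiation rules, sample size and alpha stay as they are, and no visit or test is added. The costs are a protocol amendment, which needs ethics approval before use if it is judged substantial, and some unknown-reason dropouts being counted as worsening. On the plan's 10% dropout spread evenly, that reclassification could involve at most about 2 to 5 participants across both arms.

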### Randomisation and allocation

After confirmation of eligibility and completion of baseline assessments, participants are randomised in a 1:1 ratio to either discontinuation or continuation of riociguat. Randomisation is performed in CastorEDC (Ciwit B.V., Amsterdam, The Netherlands) using block randomisation with variable block sizes. Stratification is applied by riociguat dose at inclusion (daily dose of <6 mg vs ≥6 mg) and time since last BPA, distinguishing incident patients (scheduled for RHC as part of standard clinical follow-up) from prevalent patients (those in long-term follow-up, screened by transthoracic echocardiography (TTE); last RHC performed more than 3 months ago). Due to the nature of the intervention, the trial is conducted as an open-label study. Blinding was considered impractical given the recognisable side effects of riociguat and the objective nature of the majority of primary and key secondary outcomes. However, all physicians performing outcome measurements will be blinded to treatment allocation.

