### Non-inferiority margin

The NI margin for mPAP was set at 4 mmHg. This margin reflects a clinically relevant rebound increase while remaining below established treatment thresholds. In our target population, the mean mPAP was approximately 23.6 mmHg. An NI margin of 4 mmHg ensures that the upper limit of the 95% CI remains below 30 mmHg, the threshold for initiating PH therapy (online supplemental figure).^1^

To place this margin in the context of expected interindividual variability, the distribution of mPAP at follow-up was estimated using a pooled SD derived from longitudinal haemodynamic data. Based on this variability, 97.5% of patients are expected to have an mPAP below 38 mmHg at follow-up (23.6+4 + 2×4.9), a threshold that has been associated with worse long-term outcomes in CTEPH.^19^ This approach aims to preserve haemodynamic safety at both the group and individual patient level (online supplemental figure).

The SD of mPAP was estimated from preliminary cohort data in patients meeting the inclusion criterion of mPAP <30 mmHg at 6 months post-BPA (SD 3.43 mmHg). To account for longitudinal variability beyond 6 months, unpublished follow-up data from BPA-treated and PEA-treated patients followed from 6 to 18 months post-intervention, were incorporated (n=40), yielding an SD of mPAP change of 3.8 mmHg, with a correlation of −0.08. The pooled SD was calculated as: $\sqrt{\sigma^{2}combi}=\;\sqrt{3.43^{2}+\;3.8^{2}+\;\left(2\times -0.08\times \;3.43\times \;3.8\right)}=4.9$, which was used for both the sample size calculation and estimation of interindividual variability.

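### The two measures listed for whether TTE can replace RHC are unlikely to answer it: correlation cannot see a low-reading TTE, and the ≥38 mmHg miss count is expected to rest on fewer than one case

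*Protocol article*

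**What the plan says.** Under feasibility, Table 1 (Objectives and endpoints) asks: "Is TTE sufficient to replace RHC at the end of study follow-up". Two measures follow.

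- The first is "The correlation between TTE and RHC parameters", followed by "Right ventricular systolic pressure Tricuspid annular plane systolic excursion". The table was flattened in extraction. Reading RVSP and TAPSE as the TTE parameters to be correlated is natural, but inferred.
- The second is "Proportion of participants missed by TTE with mPAP ≥38 mmHg at 16 weeks RHC".

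The figures that govern how many participants will reach 38 mmHg are in the section Non-inferiority margin: "In our target population, the mean mPAP was approximately 23.6 mmHg"; "The NI margin for mPAP was set at 4 mmHg"; and, with an SD of 4.9 mmHg, "97.5% of patients are expected to have an mPAP below 38 mmHg at follow-up (23.6+4 + 2×4.9"). The section Sample size calculation sets the total at 74, randomised 1:1. Follow-up and safety monitoring has RHC and TTE done at baseline and again at week 16.

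**The concern.** The question is one of replacement: could TTE be used instead of RHC after riociguat is stopped? That needs evidence that TTE gives the same pressure, or that it finds the participants whose pressure is raised. Correlation gives neither, because it measures only how closely two quantities follow a straight line, whatever its intercept or (positive) slope. A TTE pressure 10 mmHg too low in everyone has the same correlation as an unbiased one. TAPSE is a distance with no RHC counterpart in the same units, so its correlation cannot speak to replacing a pressure measurement.

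The listed measure that could expose under-reading is the miss count at ≥38 mmHg. If almost nobody reaches 38 mmHg, that count is empty and the correlation is the only informative number left. A high correlation might then be read as support for dropping RHC although nothing in the analysis had tested for bias or missed cases.

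**Working it through.** **Inputs.** Mean mPAP 23.6 mmHg, margin 4 mmHg, SD 4.9 mmHg (Non-inferiority margin); 74 participants, 1:1, so 37 per arm (Sample size calculation; Randomisation and allocation). Assumption: week-16 mPAP is roughly normal, as the plan's own 97.5% statement implies.

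**The plan's own figure.** 23.6 + 4 + 2 × 4.9 = 37.4 mmHg, which the plan rounds up to 38. Taken at face value, at most 2.5% of a stop arm sitting at the margin reaches 38 mmHg: 0.025 × 37 = 0.9 participants.

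**Expected cases at ≥38 mmHg**, using P = 1 − Φ((38 − mean)/4.9):

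- Mean 23.6: z = 14.4/4.9 = 2.94, P = 0.16%.
- Mean 27.6: z = 10.4/4.9 = 2.12, P = 1.69%.

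| Scenario | Expected cases among 74 | Chance of none |
|---|---|---|
| Both arms at 23.6 | 74 × 0.00165 = 0.12 | (1 − 0.00165)^74 = 89% |
| Stop arm at 27.6, continuation at 23.6 | 37 × (0.0169 + 0.00165) = 0.69 | (1 − 0.0169)^37 × (1 − 0.00165)^37 = 50% |

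With no cases, the proportion missed among cases is undefined. If the denominator is all participants, the proportion is zero or close to it however TTE performs. With exactly one case, detected, the exact 95% interval for sensitivity is 2.5% to 100%. Dropout lowers the counts further.

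**Correlation under bias.** For any constant b and any k > 0, corr(X, kY + b) = corr(X, Y). This is exact and needs no assumption about TTE.

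**Illustration only.** The article gives no TTE error, bias or cut-off, so these are assumed: week-16 mPAP with mean 25.6 (midway between 23.6 and 27.6) and SD 4.9; a TTE estimate on the same scale with random error SD 4 mmHg; a cut of 30 mmHg on both. Then r = 4.9/√(4.9² + 4²) = 0.77 at every bias.

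| TTE bias (mmHg) | r | Sensitivity for mPAP ≥30 |
|---|---|---|
| 0 | 0.77 | 72% |
| −3 | 0.77 | 46% |
| −6 | 0.77 | 23% |
| −10 | 0.77 | 6% |

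A second set of assumptions (mean 27.6, error SD 3, cut 38) tells the same story and shows that the plan's second measure does respond to bias. At shifts of 0, −5 and −10 mmHg, r stays at 0.853 while the share of ≥38 mmHg cases missed goes from 31% to 83% to 99%. What the second measure lacks is cases.

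**Expected cases at ≥30 mmHg**, by the same formula:

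- Mean 23.6: z = 6.4/4.9 = 1.31, P = 9.6%.
- Mean 27.6: z = 2.4/4.9 = 0.49, P = 31.2%.
- Both arms at 23.6: 74 × 0.0958 = 7.1 cases.
- Stop arm at the margin: 37 × (0.312 + 0.0958) = 15.1 cases.

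For scale, 12 detected of 15 has an exact 95% interval of 52% to 96%, and 6 of 7 has 42% to 99.6%. These are wide, but they are estimates.

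**The case against.** The strongest objection is that Table 1 does not rest on correlation. Directly below it stands a misclassification measure, the kind that exposes a low-reading TTE. This stands: a reader might infer that the plan judges replacement by correlation alone, and the table shows otherwise. The objection does not rescue the pair, because on the plan's own mean, margin and SD the second measure is expected to have fewer than one case.

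A reader might also take the fall in sensitivity from 72% to 6% as a forecast for this trial. It is not one. Nothing in the article says that TTE reads low here or how noisy it is, and RVSP is a systolic pressure rather than an mPAP estimate. Only the invariance of r is established.

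Range restriction is a lesser point. Entry requires mPAP <30 mmHg, and prevalent patients are "screened by transthoracic echocardiography (TTE); last RHC performed more than 3 months ago". The assumed instrument with error SD 4 would give r = 0.77 at SD 4.9 and 10/√(10² + 4²) = 0.93 at SD 10.0, the spread at first BPA in Figure 1. But patients like those enrolled are the population in which replacement is asked, eligibility still rests on RHC, and no TTE screening cut-off is given. This means only that r depends on the sample, not that r here is wrong.

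Finally, limits of agreement, cut-offs and the criterion for sufficiency may be set out in the full protocol or SAP, and their absence from an article is no fault. The point concerns the two measures that are stated.

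**Conclusion.** The point holds in this form: neither listed measure, nor the two together, is likely to show whether TTE is sufficient. That correlation is blind to constant or proportional under-reading is a mathematical fact. That the ≥38 mmHg measure will have about 0.1 to 0.7 expected cases, with an 89% to 50% chance of none, rests on the plan's mean, margin and SD, a normal distribution and 37 per arm with complete data. A heavier upper tail, or a mean rise beyond the margin, would give more cases. The documents do not support the stronger statements that correlation is the only criterion or that TTE will miss most raised pressures in this trial. The endpoint is a secondary feasibility question outside the non-inferiority tests and the sample size calculation, so the primary conclusion is unaffected. It should be corrected because an answer in favour of TTE would bear on whether RHC is done after stopping.

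**What to change.** Keep the RVSP and TAPSE correlations, labelled as descriptive. State that the replacement question will be answered from:

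1. the mean difference and 95% limits of agreement between TTE and RHC systolic pressure at week 16;
2. the ROC area, and sensitivity with exact 95% confidence intervals, of the TTE measures for week-16 mPAP ≥30 mmHg, a threshold the plan already uses for eligibility and in its margin argument;
3. the existing count missed at mPAP ≥38 mmHg, reported with its denominator.

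Fix the TTE cut-off used for sensitivity and for "missed" before the data are seen, if the SAP does not already do so.

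The cost is analysis wording. TTE and RHC are already performed at baseline and week 16, so no visit or test is added; the one thing to confirm is that systolic pulmonary artery pressure is recorded at RHC, since the article names only the mean. The downside is a wide sensitivity interval with about 7 to 15 cases, so the report may have to say that the question remains open.

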### Sample size calculation

The sample size calculation was performed for the primary endpoint, mPAP at 16 weeks, and for the two secondary endpoints highest in the hierarchy (NT-proBNP and 6MWD). Sample size calculations were performed using the formula: n=f(α,β)×2×σ²/d², where f(α,β) = (Φ⁻¹(α) + Φ⁻¹(β))². For the primary endpoint (mPAP at 16 weeks), assuming a one-sided α of 0.025, power of 90%, SD of 4.9 mmHg and an NI margin of 4 mmHg, 64 participants (32 per group) are required. Allowing for a 10% dropout rate, the target sample size for the primary endpoint is 70 participants.

For NT-proBNP, a NI margin of 30% was chosen, reflecting a clinically meaningful change commonly used in PH and heart failure trials.^20–24^ NT-proBNP values from preliminary data were log-transformed (mean 5.04, SD 1.15), corresponding to a NI margin of 1.51 on the log scale. This yielded a required sample size of 26 participants (13 per group) with 90% power and one-sided α=0.025; accounting for dropout, 29 participants are required. For 6MWD, a NI margin of 15% was used, consistent with widely used definitions of clinical worsening in PAH and CTEPH trials. Using a mean of 467 m and an SD of 95 m of riociguat-treated post-BPA patients derived from a study by Wiedenroth *et al*,^25^ 66 participants (33 per group) are required with 85% power and one-sided α=0.025. After allowing for 10% dropout, 74 participants are required. As the largest sample size was required for 6MWD, the total sample size was set at 74 participants.

NT-proBNP was prioritised in the hierarchical testing strategy because it is an objective biomarker that reflects haemodynamic status. Also, the planned sample size provides greater statistical power for NT-proBNP than for 6MWD.

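### The two missed-case endpoints in Table 1 are set at mPAP ≥38 mmHg, where the plan's own figures predict about 0.1 to 0.7 cases, so they cannot show detection

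*Protocol article*

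**What the plan says.** Table 1 (Objectives and endpoints) puts two questions under feasibility.

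- The first concerns TTE: "Is TTE sufficient to replace RHC at the end of study follow-up? The correlation between TTE and RHC parameters". The parameters are right ventricular systolic pressure and tricuspid annular plane systolic excursion. The other TTE measure is "Proportion of participants missed by TTE with mPAP ≥38 mmHg at 16 weeks RHC".
- The second asks whether the stopping strategy can be implemented in practice. Its measures are "Proportion of participants missed by the clinical worsening criteria with mPAP ≥38 mmHg at 16 weeks" and participants' satisfaction.

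The proportion with mPAP ≥38 mmHg is also listed separately as a safety endpoint.

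The section Non-inferiority margin supplies the distribution. It says "In our target population, the mean mPAP was approximately 23.6 mmHg" and "The NI margin for mPAP was set at 4 mmHg". It derives an SD of 4.9 mmHg, "which was used for both the sample size calculation and estimation of interindividual variability". It then concludes that "97.5% of patients are expected to have an mPAP below 38 mmHg at follow-up (23.6+4 + 2×4.9". The 30 mmHg level is already in use as the eligibility limit (Study population) and as the treatment threshold behind the margin (Non-inferiority margin, Discussion).

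**The concern.** The margin is defended on the ground that hardly anyone reaches 38 mmHg, even if the mean rises by the whole margin. The same level is then the case definition for two endpoints about detection. A detection measure needs cases to detect, and if the margin argument is right there will be almost none.

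At stake is how the result is read. An outcome of none missed, out of zero or one case, could be taken as support for following stopped patients by TTE or by the worsening criteria, when the trial would hold almost no information on either. The correlation does not fill the gap for TTE. A TTE pressure that is biased, or that fails to flag the patients with raised pressure, can still correlate with the catheter value.

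**Working it through.** **Inputs.** Mean 23.6 mmHg, margin 4 mmHg, SD 4.9 mmHg (Non-inferiority margin). Total 74: "As the largest sample size was required for 6MWD, the total sample size was set at 74 participants". Allocation is 1:1, so 37 per arm. After 10% dropout the plan has 66 evaluable, 33 per group. Normality is assumed, as in the plan's own 2-SD argument.

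**1. The plan's figures reproduce.**
- SD = √(3.43² + 3.8² + 2 × (−0.08) × 3.43 × 3.8) = √24.12 = 4.91, stated as 4.9.
- 23.6 + 4 + 2 × 4.9 = 37.4. The normal share below 37.4 is 97.7%, and below 38 it is 98.3%. The stated 97.5% holds within rounding.

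**2. Probability of mPAP ≥38 mmHg**, P = 1 − Φ((38 − mean)/4.9).
- Mean 23.6: 1 − Φ(14.4/4.9) = 0.00165.
- Mean 27.6: 1 − Φ(10.4/4.9) = 0.0169.

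**3. Expected cases at ≥38 mmHg.**

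| Scenario | Expected cases | Chance of no case |
|---|---|---|
| No rise: 74 × 0.00165 | 0.12 | 89% |
| Full 4 mmHg rise in the discontinuation arm only: 37 × (0.00165 + 0.0169) | 0.69 | 50% |
| Same, 66 evaluable: 33 × (0.00165 + 0.0169) | 0.61 | 54% |
| Rounded 2.5% in the 37 discontinuation participants | 0.93 | 39% |
| Rounded 2.5% in all 74 (also shifts the continuation arm) | 1.85 | 15% |

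**4. What so few cases can show.** If all of k cases are detected, the exact 95% upper limit for the miss rate is 1 − 0.025^(1/k): 98% for k = 1, 84% for k = 2, 71% for k = 3.

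**5. Departures from the plan's assumptions** (assumed values; no rise to full rise).
- A heavier-tailed t distribution with 5 degrees of freedom and the same SD gives 0.5 to 1.0 cases.
- An SD of 6 mmHg gives 0.6 to 1.8.
- A 6 mmHg rise at SD 4.9 gives 1.7.
- Five expected cases in 37 would need a discontinuation mean near 32.6 mmHg, a 9 mmHg rise.

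**6. The same calculation at ≥30 mmHg.**
- Mean 23.6: 1 − Φ(6.4/4.9) = 0.0958. Mean 27.6: 1 − Φ(2.4/4.9) = 0.312.
- No rise: 74 × 0.0958 = 7.1 cases. Full rise: 37 × (0.0958 + 0.312) = 15.1 cases.
- If every case is detected, the exact 95% lower limit for sensitivity is 0.025^(1/7) = 59% with 7 cases and 0.025^(1/15) = 78% with 15.

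**7. The correlation.** An assumed r of 0.7 in 66 participants has a 95% CI of 0.55 to 0.81. It is estimable, but this is precision about association only.

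**The case against.** A reader might go further than the documents allow, and these objections stand.

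- *That the feasibility questions cannot be answered at all, or rest wholly on 38 mmHg.* Table 1 asks only about TTE as a replacement for RHC, and for that it also lists correlations that use every participant. The worsening criteria sit under a separate question about implementation, which also has a satisfaction endpoint.
- *That the ≥38 mmHg safety proportion is equally defective.* It is not. Few expected events are no fault in a safety endpoint placed at a prognostic level. Zero of 37 still bounds the risk at 1 − 0.025^(1/37) = 9.5%. Moving that threshold would change what the endpoint measures and is a clinical judgement.
- *That fewer than one case is certain.* It is a model prediction. The plan's rounded 2.5% applied to everyone gives 1.85, and a rise well beyond the margin would give more.

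Two further objections stand only in part. Read as a share of all participants, zero missed of 66 has an upper limit of 5.4%. That has some bearing on feasibility, but it mainly reflects how rare the event is and would look much the same for a test that detected nothing. These items also lie outside the testing hierarchy and carry no power claim. That limits the weight of the point, but not the fact that each is the only listed measure of detection for its question.

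**Conclusion.** The point holds for the two missed-case endpoints. On the plan's own mean, SD and allocation, 0.12 to 0.69 participants are expected at ≥38 mmHg, and under 2 on every reading of the stated 2.5%. The probable result is zero or one case, from which no useful miss rate follows. The conclusion rests on approximate normality and a rise no larger than the margin. Moderately heavier tails, an SD of 6 mmHg or a 6 mmHg rise do not overturn it. For TTE, the remaining measure is a correlation, which does not show agreement or detection and so does not by itself answer whether TTE can stand in for RHC. The non-inferiority conclusion and the ≥38 mmHg safety proportion are unaffected. This is worth correcting before analysis, but it does not threaten the main result.

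**What to change.** - Leave the ≥38 mmHg safety proportion as it is.
- Report the two missed-case items at ≥38 mmHg as descriptive counts, with the number of participants at or above 38 mmHg as the denominator.
- Add the same two measures at mPAP ≥30 mmHg at 16 weeks, as sensitivity and specificity with exact CIs, using whatever TTE rule the full protocol defines. Here 30 mmHg serves only as an analysis threshold that the plan already uses; it implies no treatment rule.
- Add limits of agreement between TTE-derived and catheter systolic pressure beside the correlation.

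The cost is a change of analysis wording, since RHC and TTE are both already scheduled at 16 weeks. There are three downsides. Precision stays modest at about 7 to 15 cases. Some participants at ≥30 mmHg will be there through ordinary variation, since the model predicts about 7 with no drug effect at all. A participant who meets the worsening criteria and restarts riociguat may also have a lower pressure by week 16, so the sensitivity of those criteria should be reported together with the number of restarts.
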